### **9.3 Interim Analyses**

Two interim analyses are planned for this study.

The first interim analysis will be conducted on bronchoscopy samples and will be performed after the first 15 healthy subjects and the first 15 asthma subjects of at least one severity group have undergone bronchoscopy to determine whether to continue with additional bronchoscopy sampling. No formal database lock is required for this interim analysis. Any asthma severity group that has completed bronchoscopies in 15 subjects would be included in the analysis. Endobronchial biopsy specimens will be submitted for RNA extraction and gene expression microarray analysis to evaluate the level of variability within the cohort. If the analysis reveals that the median coefficient of

variation for probe-sets from gene expression microarray analysis exceeds 60% in both the asthma groups and the healthy control group, then additional bronchoscopies will not be conducted. In addition, if it is determined that the overall quality of the RNA obtained from bronchoscopy samples is inadequate, then additional bronchoscopies will not be conducted. While the interim analysis is being performed, the screening of subjects for bronchoscopies and performance of bronchoscopies will be stopped for subjects in the healthy cohort and the asthma severity group(s) included in the interim analysis. Enrollment of asthma subjects for bronchoscopy in the other severity groups will not exceed 15 subjects per group until the interim analysis is complete. Enrollment of asthma subjects not undergoing bronchoscopy will not be interrupted for the purpose of the interim analysis.

The second interim analysis will be conducted upon completion of last bronchoscopy procedures in the last subject participating in the bronchoscopy portion of the study. The main goal of this interim analysis will be biomarker evaluation of the samples collected at the screening, baseline, and bronchoscopy visits and will include but will not be limited to microarray analysis of RNA isolated from samples and soluble analyte analysis of serum and IS samples. To support this analysis a data base lock will be performed to provide demographic and clinical information for the planned biomarker analyses. The output of this interim analysis will include, but not be limited to, study population results, safety results, information on asthma characteristics of mild, moderate and severe cohorts and their respective clinical parameters, differences in biomarkers across cohorts, identification of biomarker-defined subsets across and within cohorts, correlations of biomarker, clinical, and demographic parameters, and correlations of biomarker measurements across sampling matrices.

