### **3 OVERVIEW OF STUDY DESIGN**

Approximately 180 subjects will be enrolled with up to 50 subjects in each of the mild, moderate and severe asthma cohorts and 30 subjects in the healthy subject cohort. There is no study related therapeutic intervention and this protocol will not restrict or introduce any therapeutic interventions including medications. All subjects will continue to be managed by their personal physicians.

All eligible subjects will be enrolled during screening visits and then undergo the study procedures which will include medical history and physical exam, patient reported outcomes and questionnaires for asthmatic subjects only, pulmonary function testing (PFT), assessment of airway reactivity, blood for routine laboratory tests, biomarkers and DNA evaluation (in consenting subjects), induced sputum collection and exhaled nitric oxide collection. A bronchoscopy will be performed on up to 30 healthy subjects and on up to 30 asthma subjects from each of the asthma severity cohorts. The healthy subject cohort will be evenly split into two age ranges of 18 to 36 years of age or 37 to 55 years of age. All subjects with asthma will have 3 subsequent visits at 3, 6 and 12 months after the baseline visit for repeat sample collection (PFT, exhaled nitric oxide (NO), blood, urine and sputum only) to evaluate stability of phenotypes. The overall study schema is provided in Figure 1.

Two database locks are planned: an interim database lock after completion of the last bronchoscopy procedures for the last subject receiving a bronchoscopy; a second database lock will occur at the end of the study after the last scheduled visit has occurred for the last subject in the study.

[figure not shown]

 30 subjects from each asthma severity group and 30 healthy subjects, within 5-14 days after baseline

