## **11 ETHICAL ASPECTS**

### **11.1 Study-Specific Design Considerations**

None of the procedures may necessarily benefit the subjects and there is the potential of adverse events in particular related to the procedures. For asthmatic subjects, it is possible that knowledge of the inflammatory phenotype of the subjects could help their physician guide future therapy.

For subjects who are undergoing sputum induction, common expected effects include salty taste, retching, vomiting coughing, dizziness and faintness. Most of these are mild and self-limited. However, depending on the severity of these symptoms, the PI may decide to record an AE. Subjects, particularly those with asthma may experience dyspnea, wheeze due to bronchospasm. Again, in most cases the symptoms are mild and self-limiting. The PI will decide as to whether such asthma symptoms require recording as an adverse event on a case-by-case basis. The overall risk of sputum induction is low and there are no reported cases of death (see Study Reference Manual for safety monitoring). If a subject has an unnoticed infectious disease (eg, active TB), there may be a risk of exposing study personnel to infection.

The bronchoscopy procedure consists of the administration of lidocaine, atropine and agents used for conscious sedation and the procedure itself. There are potential adverse events that arise from lidocaine including lidocaine toxicity which is dose related and can be prevented by recording the amounts administered and setting an upper limit (see Study Reference Manual). Atropine may result in tachycardia, worsening of glaucoma, and urinary retention. Subjects should be screened for these conditions before bronchoscopy. The medications used for conscious sedation vary from center to center but include opiates and short-acting intravenous benzodiazepines. The risks of these agents include allergic reactions, excessive sedation with respiratory depression and hypoxemia, hypercarbia and apnea. Careful titration of medications and monitoring of all subjects by skilled personnel including continuous ECG and oximetry should help avoid these complications.

The bronchoscopy procedure includes insertion of the scope via a naris or the oral cavity and hence through the vocal cords into the lower respiratory tree. While an extremely

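### Section 9.3 states no hold at 15 bronchoscopies for the cohort that meets its half of the interim trigger first, so that cohort may pass 15 before the decision on further sampling

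*Protocol*

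**What the plan says.** All the rules at issue stand in Protocol section 9.3 (Interim Analyses), in the paragraph on the first interim analysis.

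- **Purpose.** The analysis is done "to determine whether to continue with additional bronchoscopy sampling".
- **Trigger.** It is performed "after the first 15 healthy subjects and the first 15 asthma subjects of at least one severity group have undergone bronchoscopy". Both halves must be met.
- **Who is analysed.** The healthy cohort, and on the asthma side: "Any asthma severity group that has completed bronchoscopies in 15 subjects would be included in the analysis".
- **Hold for the analysed cohorts** (healthy, and each severity group that is analysed). "While the interim analysis is being performed, the screening of subjects for bronchoscopies and performance of bronchoscopies will be stopped".
- **Cap for the remaining groups.** "Enrollment of asthma subjects for bronchoscopy in the other severity groups will not exceed 15 subjects per group until the interim analysis is complete".

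The overall ceiling is in section 3: "A bronchoscopy will be performed on up to 30 healthy subjects and on up to 30 asthma subjects from each of the asthma severity cohorts". Section 8.2 replaces subjects who withdraw before bronchoscopy up to that same ceiling and mentions no pause at 15. Section 9.3 ends further bronchoscopy if the median coefficient of variation of the probe-sets exceeds 60% in both the asthma groups and the healthy group, or if overall RNA quality is judged inadequate.

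**The concern.** The two holds begin at different times. The cap on the other severity groups applies up to completion of the analysis, so it already binds beforehand. The hold on the analysed cohorts binds only during the analysis, and the analysis cannot start until the slower half of the trigger is met. A cohort that reaches 15 early is thus under no written instruction to pause. The cohorts on which the decision rests are held less tightly than those left out of it.

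What is at stake is the use of the look itself. It exists to decide whether bronchoscopies beyond the first 15 are worth doing. If the faster cohort is well past 15 by then, a decision to stop spares fewer of its subjects, or none. Section 11.1 says "None of the procedures may necessarily benefit the subjects", and goes on to state that complications of bronchoscopy can be serious and, rarely, fatal.

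**Working it through.** **1. The ceiling.** Section 9.2 needs at least 5 subjects in a subset that makes up 20% of a group: 5 / 0.20 = 25. Raised by 20% this gives 25 × 1.20 = 30, the stated figure. (Dividing by the 80% adequate-sample rate gives 25 / 0.80 = 31.25; that is a separate matter and does not affect this point.) Four groups of 30 make 120 planned bronchoscopies.

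**2. Which rule binds before the trigger is met.**

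| Cohort | Hold during the analysis | Cap of 15 until completion | Ceiling while waiting |
|---|---|---|---|
| Healthy | yes, but not yet started | no, it is not a severity group | 30 |
| First severity group to reach 15 | yes, but not yet started | no, it is an analysed group and not one of the others | 30 |
| Remaining severity groups (narrower reading) | not relevant | yes | 15 |

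**3. Largest counts the text allows before the trigger, on the narrower reading.**
- Healthy fast, each asthma group one short: 30 + 3 × 14 = 72.
- Healthy one short, one severity group fast, the other two at their cap: 14 + 30 + 2 × 15 = 74.

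By the time of the decision either path can reach 30 + 3 × 15 = 75. With every cohort held at 15 the maximum is 4 × 15 = 60. The excess is 75 − 60 = 15, all in one cohort, because the slower half of the trigger stands at exactly 15 when the hold begins.

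**4. Likely size, by simulation.** The protocol states no recruitment rates, so everything here is assumed: Poisson accrual, three asthma groups at equal rates, at least 20,000 runs per scenario. Trigger time T = max(time of the 15th healthy bronchoscopy, earliest time at which any severity group has its 15th). Extra procedures = bronchoscopies beyond 15 at T in the healthy cohort and in the first severity group to reach 15, each truncated at 30, with the other two groups capped at 15.

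| Healthy rate relative to each asthma group | Mean extra before the trigger |
|---|---|
| 1× | about 4.3 in total (0.6 healthy + 3.7 asthma) |
| 2× | about 8, nearly all healthy |
| 3× | about 13.5, healthy |
| 0.5× | about 13, asthma |

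At equal rates some cohort passes 15 before the trigger in about 86% of runs, but one reaches 30 in no more than about 3%. The healthy cohort reaches 30 in about 19% of runs at 2× and about 73% at 3×.

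**The case against.** Five replies deserve weight.

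- **A standing cap exists.** A reader might infer that section 9.3 freezes bronchoscopy only while the analysis runs, for everyone. It does not: the other severity groups may not pass 15 before completion. This stands, and it confines the point to the healthy cohort and the first severity group to reach 15.
- **The asthma figures depend on the reading.** One could argue that every severity group that reaches 15 becomes an analysed group and so escapes the cap. Then up to 3 × 15 = 45 extra asthma bronchoscopies could precede the trigger (14 + 3 × 30 = 104 of 120 in all), with a mean of about 34 if healthy recruitment runs at half rate. The narrower reading is the more natural. The cap is in force beforehand, and a group held at 15 has still completed 15 and can be analysed, so the two sentences fit together. The documents do not support the larger figures as the expected case.
- **Reaching 30 is an extreme.** This stands. It takes unequal accrual, and nothing in the protocol makes one ratio likelier than another. Passing 15, however, does not take unequal accrual.
- **The harm is conditional.** This also stands. The extra procedures lie within the planned 30 per group. If the stop does not fire they are planned procedures done earlier, and their samples feed the second interim analysis. The protocol gives no probability that the stop will fire. The look concerns feasibility and is not a safety rule.
- **The intent is plain.** Probably a pause at 15 was meant. But the same paragraph writes an explicit cap and gives it only to the other groups, so a site that follows the text has no instruction to pause the healthy cohort. This is a rule for sites, which section 9.3 itself sets, and not an analysis detail to leave for later.

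**Conclusion.** The gap is real but narrow. The half of the trigger that is met first has no stated hold between its 15th bronchoscopy and the start of the analysis. The healthy cohort is the firmest case, since a cap on severity groups cannot reach it on any reading. The first severity group to reach 15 is open in the same way when the healthy cohort lags.

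By the wording, at most 15 bronchoscopies in one cohort can precede the decision that should govern them. Expected numbers run from about 4 in total at equal rates to about 8 healthy at 2× and about 13 asthma at 0.5×. These rest on assumed Poisson accrual and the narrower reading. It would be wrong to conclude that subjects will undergo needless procedures: the extra bronchoscopies are avoidable only if the coefficient-of-variation or RNA-quality criterion is met. The text should still be corrected, because the change is small and the procedure is invasive and without expected benefit to the subject.

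**What to change.** Keep the existing stop on both screening for and performance of bronchoscopies, but let it begin for each cohort when that cohort reaches 15. Suggested wording for section 9.3:

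*No cohort (healthy, mild, moderate or severe) will exceed 15 bronchoscopies until the first interim analysis is complete and the decision to continue has been made; screening for bronchoscopy in a cohort will stop once enough subjects are in process to reach 15.*

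The screening clause matters. A bare cap on procedures in place of both present sentences would drop the current stop on screening, and subjects could be screened and undergo sputum induction for a bronchoscopy that is on hold. The trigger, the two stopping criteria and the enrolment of asthma subjects who do not undergo bronchoscopy stay as they are.

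The cost is a sentence in section 9.3 and some waiting, since a faster cohort pauses at 15 until the slower one catches up and the decision is made. Subjects already between screening and bronchoscopy when the hold begins also need a stated route. Under section 7.2.2, a healthy subject without bronchoscopy within 14 + 14 = 28 days of baseline is discontinued. An asthma subject past 28 days may move to the non-bronchoscopy cohort, or is discontinued if that cohort is full. The hold and these limits must be reconciled in the same amendment.

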#### **9.4 Biomarker Data Analyses**

The biomarker data and analyses will be reported in an independent technical report.

#### **9.5 Safety Analyses**

##### **Adverse Events**

In general, adverse events will be collected when these arise from study procedures (eg induced sputum, bronchoscopy, methacholine challenge test or blood draw). For an example, an asthma exacerbation that occurs after a bronchoscopy and that in the opinion of the investigator is related to the procedure should be recorded as an AE. The original terms used in the CRFs by investigators to identify adverse events will be coded using the MedDRA. All reported adverse events with onset during the study will be included in the analysis. All adverse events reported from both healthy subject and asthmatic subject populations will be listed.

Special attention will be given to those subjects who died, or who experienced a severe or a serious adverse event (eg, summaries, listings, and narrative preparation may be provided, as appropriate).

### **Vital Signs**

Descriptive statistics of temperature, pulse and blood pressure (systolic and diastolic) values, and changes from baseline will be listed at each scheduled time point.

## **10 ADVERSE EVENT REPORTING**

Timely, accurate, and complete reporting and analysis of safety information from clinical studies are crucial for the protection of subjects, investigators, and the sponsor, and are mandated by regulatory agencies worldwide. The sponsor has established SOPs in conformity with regulatory requirements worldwide to ensure appropriate reporting of safety information; all clinical studies conducted by the sponsor or its affiliates will be conducted in accordance with those procedures.

### **10.1 Definitions**

#### **10.1.1 Adverse Event Definitions and Classifications**

##### **Adverse Event**

An adverse event is any untoward medical occurrence in a clinical study subject administered a medicinal (investigational or non-investigational) product or underwent a study procedure. An adverse event does not necessarily have a causal relationship with the treatment. An adverse event can therefore be any unfavorable and unintended sign (including an abnormal finding), symptom, or disease temporally associated with the use of a medicinal (investigational or non-investigational) product or study procedure, whether or not related to that medicinal (investigational or non-investigational) product or study procedure. (Definition per International Conference on Harmonisation [ICH]).

As no therapeutic intervention is involved with this study, only events temporally associated with a study procedure and determined to be possibly, probably or very likely related to a study procedure including spirometry, bronchoscopy, induced sputum, methacholine challenge and blood collection will be reported as adverse events.

This includes any occurrence that is new in onset or aggravated in severity or frequency from the baseline condition, or abnormal results of diagnostic procedures, including laboratory test abnormalities.

Note: The sponsor collects adverse events starting with the signing of the informed consent form (refer to Section 10.2.1, All Adverse Events, for time of last adverse event recording).

### **Serious Adverse Event**

A serious adverse event as defined by ICH is any untoward medical occurrence that meets any of the following conditions:

- Results in death
- Is life-threatening  
(The subject was at risk of death at the time of the event. It does not refer to an event that hypothetically might have caused death if it were more severe.)
- Requires inpatient hospitalization or prolongation of existing hospitalization
- Results in persistent or significant disability/incapacity, or
- Is a congenital anomaly/birth defect

Note: Medical and scientific judgment should be exercised in deciding whether expedited reporting is also appropriate in situations other than those listed above. For example, important medical events may not be immediately life threatening or result in death or hospitalization but may jeopardize the subject or may require intervention to prevent one of the outcomes listed in the definition above (eg, suspected transmission of an infectious agent by a medicinal product is considered a serious adverse event). Any adverse event is considered a serious adverse event if it is associated with clinical signs or symptoms judged by the investigator to have a significant clinical impact.

### **10.1.2 Attribution Definitions**

#### **Not related**

An adverse event that is not related to procedures in this study.

#### **Doubtful**

An adverse event for which an alternative explanation is more likely, eg, concomitant drug(s), concomitant disease(s), or the relationship in time suggests that a causal relationship to a study procedure is unlikely.

#### **Possible**

An adverse event that might be due to a study procedure. An alternative explanation, eg, concomitant drug(s), concomitant disease(s), is inconclusive. The relationship in time is reasonable; therefore, the causal relationship cannot be excluded.

#### **Probable**

An adverse event that might be due a study procedure. The relationship in time is suggestive. An alternative explanation is less likely, eg, concomitant drug(s), concomitant disease(s).

### **Very likely**

An adverse event that is listed as a possible adverse reaction and cannot be reasonably explained by an alternative explanation, eg, concomitant drug(s), concomitant disease(s). The relationship in time is very suggestive (eg, it is confirmed by dechallenge and rechallenge).

#### **10.1.3 Severity Criteria**

An assessment of severity grade will be made using the following general categorical descriptors:

**Mild:** Awareness of symptoms that are easily tolerated causing minimal discomfort and not interfering with everyday activities.

**Moderate:** Sufficient discomfort is present to cause interference with normal activity.

**Severe:** Extreme distress causing significant impairment of functioning or incapacitation. Prevents normal everyday activities.

The investigator should use clinical judgment in assessing the intensity of events not directly experienced by the subject (eg, laboratory abnormalities).

### **10.2 Procedures**

#### **10.2.1 All Adverse Events**

Only adverse events related to the study procedures, whether serious or non-serious, will be reported from the time a signed and dated informed consent form is obtained until completion of the last study-related procedure (may include contact for follow-up of safety). Serious adverse events, including those spontaneously reported to the investigator within 30 days after the last study procedure, must be reported using the Serious Adverse Event Form. The sponsor will evaluate any safety information that is spontaneously reported by an investigator beyond the time frame specified in the protocol.

All events related to study procedures that meet the definition of a serious adverse event will be reported as serious adverse events. Adverse events related to study procedures, regardless of seriousness or severity, must be recorded using medical terminology in the source document and the CRF. Whenever possible, diagnoses should be given when signs and symptoms are due to a common etiology (eg, cough, runny nose, sneezing, sore throat, and head congestion should be reported as “upper respiratory infection”). Investigators must record in the CRF their opinion concerning the relationship of the adverse event to study procedures. All measures required for adverse event management must be recorded in the source document and reported according to sponsor instructions.

The sponsor assumes responsibility for appropriate reporting of study procedure related adverse events to the regulatory authorities if required. The investigator (or sponsor where required) must report these events to the appropriate Independent Ethics Committee/Institutional Review Board (IEC/IRB) that approved the protocol unless otherwise required and documented by the IEC/IRB.

Subjects (or their designees, if appropriate) must be provided with a “study card” indicating the study number, the investigator’s name and a 24-hour emergency contact number.

